10.4.2 Secondary Outcomes

Dichotomous outcomes (e.g., PTB at <28, <32, <37 weeks; PPROM; chorioamnionitis; neonatal survival; etc.) will be analyzed similarly to the primary outcome, presenting RR with 95% CI and using Chi-square or Fisher's exact test.

Continuous outcomes:

Normally distributed variables (e.g., gestational age at delivery in the emergency cohort PP analysis) will be presented as mean ± SD and analyzed with Independent Samples t-tests, reporting the mean difference with 95% CI.

Non-normally distributed variables (e.g., gestational latency, GA at delivery in the therapeutic cohort) will be presented as median (Q1, Q3) and analyzed with the Wilcoxon rank-sum test, with the median difference and its 95% CI calculated via the Hodges-Lehmann method.

**10.5 Time-to-Event Analysis**

Time-to-event data (gestational age at delivery) were analyzed using Kaplan-Meier survival curves and compared with the log-rank test. Participants who did not experience the primary event (spontaneous preterm birth <34 weeks) were administratively censored. Specifically, censoring occurred at the gestational age of term delivery, medically indicated (iatrogenic) delivery, study withdrawal (e.g., due to protocol violations or subsequent ineligibility), or loss to follow-up (last known gestational age with confirmed pregnancy status).

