**10.0 Statistical Analysis Plan**

**10.1 Analysis Principles**

The primary analysis will be performed according to the intention-to-treat (ITT) principle, including all randomly assigned participants in the groups to which they were originally allocated.

A supporting per-protocol (PP) analysis will also be conducted, which excludes participants who did not receive the allocated intervention or who had major protocol violations.

A two-sided p-value of less than 0.05 will be considered statistically significant for the primary outcome. All analyses will be performed using SPSS software (version 26.0, IBM SPSS, Inc, Armonk, NY).

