**10.2 Handling of Missing Data**

For the primary and secondary outcome, if data are missing, a conservative approach will be applied by imputing the missing participants as having experienced the event in the primary ITT analysis.

The PP analysis will simply exclude participants with missing primary outcome data.

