**10.4 Analysis of Outcomes**

10.4.1 Primary Outcome

The primary outcome, spontaneous PTB <34 weeks, is a dichotomous variable.

It will be compared between the two-stitch and one-stitch groups within each stratum using a Chi-square test or Fisher's exact test as appropriate.

The relative risk (RR) with a 95% confidence interval (CI) will be calculated as the primary measure of effect size.

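### The time-to-event analysis in section 10.5 is labelled gestational age at delivery but counts only spontaneous birth before 34 weeks, censors a competing event, and censors withdrawn women contrary to sections 10.1 and 10.2

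*Protocol*

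**What the plan says.** Section 10.5 of the protocol names the variable and the method: "Time-to-event data (gestational age at delivery) were analyzed using Kaplan-Meier survival curves and compared with the log-rank test". It then defines the event and the general rule: "Participants who did not experience the primary event (spontaneous preterm birth <34 weeks) were administratively censored". The censoring times follow: "censoring occurred at the gestational age of term delivery, medically indicated (iatrogenic) delivery, study withdrawal (e.g., due to protocol violations or subsequent ineligibility"), and finally loss to follow-up, at the last gestation with a confirmed ongoing pregnancy. No competing-risk method is named.

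Three other sections bear on the same women:

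- Section 10.1: "The primary analysis will be performed according to the intention-to-treat (ITT) principle, including all randomly assigned participants". Violators leave only in the supporting per-protocol analysis, which "excludes participants who did not receive the allocated intervention or who had major protocol violations".
- Section 10.2 handles missing primary and secondary outcomes by "imputing the missing participants as having experienced the event in the primary ITT analysis".
- Section 4.2(d) and (e) list indicated preterm birth and loss to follow-up among the exclusion criteria, although both can only arise after enrolment.

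The primary comparison is a different analysis. Section 10.4.1 states: "It will be compared between the two-stitch and one-stitch groups within each stratum using a Chi-square test or Fisher's exact test as appropriate", with a relative risk as the effect measure.

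**The concern.** The protocol itself fixes the event and the censoring rule, so this is not a detail left to a later document. Three things go wrong if the rule is followed as written.

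1. **Label and content differ.** A curve that drops only at spontaneous births before 34 weeks carries no information on when the other women delivered. Gestational age at delivery is a separate secondary outcome in section 2.2, and a reader of the figure would take the curve to show it.
2. **A competing event is censored.** A woman delivered for medical indication at, say, 31 weeks can no longer have a spontaneous birth before 34 weeks. Kaplan-Meier treats her as though she still could, so the curve's complement is not a risk.
3. **Withdrawal is censored.** Withdrawal for a protocol violation or later ineligibility happens after randomisation and may depend on arm or prognosis. Calling it administrative does not make it non-informative. The analysis carries no per-protocol label, yet it stops counting women whom intention-to-treat would keep.

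At stake is a published figure that may disagree with the trial's own primary result at 34 weeks for reasons unrelated to treatment.

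**Working it through.** **The plan's own figure.** The protocol gives no number for the time-to-event analysis. Its sample size of 44 for the emergency stratum rests on the binary endpoint (89.5% versus 42.1%, 90% power, two-sided 0.05). It reproduces to within two patients: 23 per arm, 46 in total, with continuity correction; Fisher power at 22 per arm is 89.8%. This point does not touch it.

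**Check 1: label against event.** On an invented data set of 25 women per arm, the 10.5 rule (event = birth before 34 weeks, others censored) gives a log-rank chi-square of 2.622. Counting every delivery as an event, which is the analysis the label implies, gives 0.080 on the same data. The values mean nothing in themselves; they show that the two analyses answer different questions.

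**Check 2: competing event.** Let *cs* be the true proportion with spontaneous birth before 34 weeks and *ci* the proportion with indicated birth before 34 weeks. Both are assumed, since the protocol gives no indicated rate. With proportional cause-specific hazards:

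- total cumulative hazard H = −ln(1 − cs − ci)
- 1 − KM = 1 − exp(−H × cs/(cs + ci))

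| cs | ci | H | cs/(cs+ci) | 1 − KM | Excess |
|---|---|---|---|---|---|
| 40% | 5% | 0.598 | 0.889 | 41.2% | 1.2 points |
| 40% | 10% | 0.693 | 0.800 | 42.6% | 2.6 points |
| 40% | 20% | 0.916 | 0.667 | 45.7% | 5.7 points |

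A cross-check from the other direction takes section 7's two rates as illustrative values of 1 − KM, with hs = −ln(1 − that value) and hi = −ln(1 − net indicated risk). The actual incidence is hs/(hs + hi) × (1 − exp(−hs − hi)). For net indicated risks of 5%, 10% and 15%, a 1 − KM of 42.1% corresponds to 41.1%, 40.1% and 39.1%, and a 1 − KM of 89.5% to 88.0%, 86.5% and 84.9%. The excess is about 1 to 5 points.

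**Check 3: withdrawn violators.** Take 25 women in an arm (section 7) and an illustrative 11 events, an intention-to-treat risk of 11/25 = 44.0%. Suppose *k* violators are censored at entry and all later deliver spontaneously before 34 weeks. The Kaplan-Meier risk is then (11 − k)/(25 − k):

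- k = 1: 10/24 = 41.7%
- k = 2: 9/23 = 39.1%
- k = 3: 8/22 = 36.4%

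**Check 4: losses under 10.2 and 10.5.** Suppose 11 events are observed and *k* further women of the 25 are lost at entry. Section 10.2 gives (11 + k)/25 = 48.0%, 52.0%, 56.0% for k = 1, 2, 3. Section 10.5 gives 11/(25 − k) = 45.8%, 47.8%, 50.0%. Section 4.2(e) would drop these women altogether.

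**The case against.** **The log-rank test survives.** Censoring a competing event leaves a valid comparison of cause-specific hazards, provided other censoring is non-informative. This stands. A reader might infer that differing indicated rates create a spurious difference between arms. They do not for the log-rank test: arms with equal spontaneous incidence but unequal indicated rates have different cause-specific hazards. The fault lies in reading the curve as risk.

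**Spontaneous births at 34+0 to 36+6.** Because the list of censoring times omits them, a reader might infer that these women have no status. The preceding sentence in 10.5 censors everyone without the primary event. Only their censoring time is unstated, and no event can occur from 34+0 onward. Censoring them at delivery, at 34+0 or at 37+0 gave the same chi-square (2.622) and the same Kaplan-Meier values at 34 weeks (0.32 and 0.52) on the invented data.

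**The primary result is untouched.** Intention-to-treat is stated for the primary analysis, which is the chi-square or Fisher comparison. This stands. So does the point that 10.5 censors violators who are withdrawn, not every violator, and the documents do not show that every withdrawn woman's delivery date can be obtained.

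**Gestational age is analysed elsewhere.** Section 10.4.2 compares it by t-test or rank-sum test. That limits the harm of the mislabel but does not correct it.

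**Section 4.2(d) might govern.** If women with indicated preterm birth are excluded, the competing-event problem does not arise for them. But then 10.5 provides for women the trial has removed after randomisation, so the conflict remains.

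**Conclusion.** The point holds for a secondary analysis and should be corrected. The curves do not estimate gestational age at delivery. Their complement overstates the incidence of spontaneous birth before 34 weeks whenever indicated births occur earlier, by 1.2 to 5.7 points for assumed indicated rates of 5% to 20% and a true incidence of 40%. The direction is certain; the size depends on rates the protocol does not give and on proportional cause-specific hazards. Censoring at withdrawal departs from 10.1 and, in the illustration, lowers one arm's risk by about 2 to 8 points. That range takes the least favourable case, in which every withdrawn woman leaves at entry and later has the event. Sections 4.2, 10.2 and 10.5 give three different treatments of women lost to follow-up. The primary relative risk and the sample size are not affected by the rule in 10.5.

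**What to change.** Rewrite section 10.5 as follows:

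- Name the variable as time to spontaneous birth before 34 weeks.
- Keep every randomised woman in her allocated arm, including protocol violators and those later found ineligible, and follow her to delivery unless she withdraws consent.
- Censor women undelivered at 34+0 at 34+0, and only women truly lost at their last known gestation.
- Plot cumulative incidence (Aalen-Johansen) with indicated delivery before 34 weeks as a competing event, and describe the log-rank test as comparing cause-specific hazards.
- If a curve of gestational age at delivery is wanted, add one under its own label with all deliveries as events. It should supplement the trial's endpoint and not replace it.

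Then reconcile 10.5 with 4.2(d) and (e), 10.1 and 10.2, so that indicated preterm births, withdrawals and losses each have one stated treatment per analysis.

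The cost is wording, a recode of the status variable, follow-up of withdrawn women where consent allows, and possibly a second software package for cumulative incidence.

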**10.6 Subgroup and Other Analyses**

The primary analysis is stratified by indication (Therapeutic vs. Emergency), which serves as a pre-specified subgroup analysis.

No other subgroup or sensitivity analyses were pre-specified in the statistical analysis plan for this initial trial.

No interim analyses for efficacy or futility were planned or conducted.

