**3.0 Trial Design**
A single-centre, stratified, parallel-group, randomised, controlled, superiority trial. The study will be conducted at Fujian Maternity and Child Health Hospital, Fuzhou, China.

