**7.0 Sample Size Calculation**

Based on historical data[1], the expected incidence of PTB <34 weeks was 89.5% in the emergency one-stitch group and 42.1% in the emergency two-stitch group. Assuming a power of 90% and a two-sided alpha of 0.05, a sample size of 44 patients was required for the emergency stratum. Accounting for a 5% dropout rate, a minimum of 46 patients per stratum (therapeutic and emergency) will be recruited, leading to a total target enrolment of 100 participants (50 per stratum, 25 per treatment arm within each stratum).

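### Section 10.6 calls the indication strata a subgroup analysis, but the protocol plans only two separate tests, with no estimate of whether the effect differs by indication and no stratum-adjusted RR over all 100 women

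*Protocol*

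**What the plan says.** The primary outcome is spontaneous preterm birth before 34 weeks. On its comparison, Protocol 10.4.1 says "It will be compared between the two-stitch and one-stitch groups within each stratum", by chi-square or Fisher's exact test, with the RR and its 95% CI as the main effect measure. Protocol 10.6 then states: "The primary analysis is stratified by indication (Therapeutic vs. Emergency), which serves as a pre-specified subgroup analysis". The same section adds that no further subgroup or sensitivity analyses were pre-specified.

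No section gives a Mantel-Haenszel or model-adjusted RR across strata, or a treatment-by-indication term. The log-rank test in 10.5 is not described as stratified or combined.

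On size, section 7.0 says "the expected incidence of PTB <34 weeks was 89.5% in the emergency one-stitch group and 42.1% in the emergency two-stitch group" and "a sample size of 44 patients was required for the emergency stratum". It then carries the number over to both strata: "Accounting for a 5% dropout rate, a minimum of 46 patients per stratum (therapeutic and emergency) will be recruited", with a "total target enrolment of 100 participants (50 per stratum, 25 per treatment arm within each stratum"). It gives no event rate or effect for the therapeutic stratum.

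**The concern.** Section 1.0 presents stratification by surgical indication as what earlier randomised evidence lacks, so readers will set the two strata side by side. The plan gives them two RRs and two p-values but no estimate of the contrast between them. One p-value below 0.05 and the other above it does not test whether the effects differ. That pattern can arise simply because one stratum has fewer events and hence less power.

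Here the imbalance is foreseeable. Both strata have 25 women per arm, the size was derived from emergency rates only, and section 1.0 singles out emergency cases as the women who still deliver preterm. The risk is a conclusion that two stitches help in emergency cerclage but not in therapeutic cerclage, when the therapeutic stratum was merely uninformative.

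This is not a detail left to a separate document. Section 10.0 is headed as the statistical analysis plan, and 10.6 closes the list of further subgroup analyses.

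**Working it through.** **Inputs from the Protocol.** Emergency risks 89.5% (one-stitch) and 42.1% (two-stitch), two-sided alpha 0.05, power 90%, 44 patients (7.0); 25 per arm per stratum (7.0, 8.1); chi-square test, or Fisher if an expected count is below 5 (10.4.1, with the switching rule from 10.3).

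**Input not in the Protocol.** The therapeutic one-stitch risk. It is assumed, and varied from 10% to 50%.

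**Step 1: the plan's own figure.** Exact power of Fisher's test at 22 per arm, 89.5% vs 42.1%, is 89.8%. This matches 44 patients at 90% power, so the emergency sample size is not in question.

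**Step 2: planned effect.** RR = 42.1/89.5 = 0.47. Odds ratio = (0.421/0.579)/(0.895/0.105) = 0.727/8.524 = 0.085. Risk difference = 89.5 − 42.1 = 47.4 points.

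**Step 3: power per stratum at 25 per arm.** All 26 × 26 pairs of event counts were enumerated under binomial sampling with the plan's test rule. Emergency power is 97.0%. For the therapeutic stratum, the two-stitch risk is 0.47 times the one-stitch risk.

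**Step 4: chance of discordance.** The strata are independent, so P(emergency significant, therapeutic not) = power(E) × (1 − power(T)).

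| Assumed therapeutic one-stitch risk | Power (T), RR 0.47 | Discordance |
|---|---|---|
| 10% | 1.4% | 0.970 × 0.986 = 96% |
| 20% | 12.2% | 0.970 × 0.878 = 85% |
| 30% | 26.8% | 0.970 × 0.732 = 71% |
| 40% | 38.9% | 0.970 × 0.611 = 59% |
| 50% | 52.5% | 0.970 × 0.475 = 46% |

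Discordance exceeds one half when the risk is below roughly 47%. The reverse pattern occurs in under 2% of trials at these risks.

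**Step 5: weaker common effects.**

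| Emergency / therapeutic one-stitch risk | Common RR | Power (E) | Power (T) | Discordance |
|---|---|---|---|---|
| 70% / 30% | 0.67 | 42.1% | 12.9% | 0.421 × 0.871 = 37% |
| 70% / 30% | 0.60 | 56.5% | 16.9% | 0.565 × 0.831 = 47% |
| 60% / 25% | 0.50 | 62.2% | 18.0% | 0.622 × 0.820 = 51% |

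With the emergency one-stitch risk kept at 89.5%, a common RR of 0.8 gives 33% to 29% over therapeutic risks of 10% to 50%.

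**Step 6: other scales.** With a common odds ratio of 0.085, discordance at therapeutic risks of 10, 20, 30, 40 and 50% is 94%, 67%, 32%, 12% and 5%. A common 47.4-point risk difference is impossible where the one-stitch risk is below 47.4%.

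**Step 7: what an interaction estimate would give.** In 100,000 simulated trials per scenario, a Wald test was applied to log RR(E) − log RR(T), with 0.5 added to counts. Under a common RR of 0.47 it rejects in 1% to 4% of trials, so it rarely supports a false difference. If two stitches do nothing in the therapeutic stratum while the planned emergency effect holds, it detects the difference in about 10%, 23%, 33%, 43% and 53% of trials at therapeutic risks of 10, 20, 30, 40 and 50%.

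**The case against.** The strongest reply is that this is in effect two parallel cohort-specific comparisons. Section 1.0 asks the question within each cohort, 2.1 makes the primary objective stratified by indication, 4.1 gives each cohort its own entry criteria, 8.1 keeps separate lists, and 10.4.1 tests within strata. On that reading the stratum RRs are the targets and a pooled RR answers a different question. This stands, and it is why the pooled RR should be supporting and not primary.

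A reader might infer that section 3.0 poses an overall superiority question that is never answered. It does not: "A single-centre, stratified, parallel-group, randomised, controlled, superiority trial" is a one-line design label and states no pooled hypothesis.

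Nor does the document say that p-values will be compared across strata. Stratum RRs with CIs will be reported, so readers will see the imprecision. That also stands: misreporting is a risk and not something the text announces. But 10.6 invites the comparison by using the subgroup label, and it gives no method for it.

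A reader might also infer that a combined test would gain power. Against a significant result in either stratum at the plan's 0.05, the Cochran-Mantel-Haenszel test has less power in the three Step 5 scenarios: 42.8% vs 49.5%, 58.3% vs 63.8% and 67.5% vs 69.0%. An advantage appears only against tests at 0.025, a split the plan does not contain. Two tests at 0.05 do carry a familywise error of up to 1 − 0.95² = 9.75%, but that is a separate matter.

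Finally, the high discordance figures depend on an assumed therapeutic risk and a constant RR. This is correct, and it limits the size of the claim.

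**Conclusion.** The point holds as a gap in what the plan fixes. The strata are labelled a subgroup analysis, the analysis consists of separate tests only, and nothing estimates the difference between indications or an adjusted RR over all 100 women.

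Discordant significance would be common with no true difference in RR: 85% to 59% of trials at assumed therapeutic risks of 20% to 40% with the planned RR of 0.47, and 37% to 51% in the moderate scenarios. These figures rest on two assumptions. The therapeutic one-stitch risk is not in the Protocol, and sameness of effect is defined on the RR scale, which 10.4.1 makes the main effect measure. They do not carry over to an equal odds ratio at risks above about 25%, or to an equal risk difference. The stronger statement, that the trial will probably mislead whenever the effect is the same in both strata, is therefore not supported.

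The defect does not invalidate the trial or its within-stratum RRs. It bears on what may be claimed about indication, and it should be settled before analysis.

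**What to change.** Keep the within-stratum RRs and tests of 10.4.1 as planned, and make three additions.

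1. In 10.6, add the ratio of the two stratum RRs with 95% CI and interaction p-value, from a modified Poisson or log-binomial model with arm, stratum and arm-by-stratum terms.
2. In 10.6, state that a difference between indications will not be inferred from one stratum being significant and the other not.
3. In 10.4.1, add a Mantel-Haenszel common RR with 95% CI over both strata, by intention to treat, as a supporting analysis.

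The cost is a few lines of text and one extra model, with no new data. The limitation is precision: because the interaction test is weak at this sample size, the ratio of RRs should be read through its CI, and the text should say that a non-significant interaction does not show equal effects. Making the pooled RR primary would change the question asked in sections 1.0 and 2.1, and is not proposed.

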**10.7 Data Presentation**

All results will be presented with the exact p-values.

Effect estimates (RR, mean difference, median difference) will be reported with their 95% CIs.

The analysis will be reported in accordance with the CONSORT guidelines.

**11.0 Ethics and Monitoring**

The study protocol was approved by the Institutional Ethics Committee of Fujian Maternity and Child Health Hospital (Approval No: 2022YJ012). Written informed consent will be obtained from all participants prior to any study procedures. The trial will be monitored by an independent data and safety committee to ensure participant safety and data integrity.

**12.0 Protocol Amendments**

Any amendments to the protocol requiring changes to study design, procedures, or informed consent will be submitted to the Ethics Committee for approval prior to implementation. Changes will also be updated in the clinical trial registry.

